#### Imaging Analyses

##### Preprocessing

Neuroimaging data will be converted from dicom to NIfTI format using the dicm2nii converter, and will then be preprocessed using different software toolboxes, largely based in SPM12 (^1^
RRID:SCR_007037), in MATLAB^®^ (2017b; The MathWorks Inc., Natick, MA, United States). The RS-fMRI data will be preprocessed and analyzed using the functional connectivity toolbox (CONN;^2^
RRID:SCR_009550). The pCASL data will be preprocessed and analyzed in ASL Perfusion MRI data processing toolbox (^3^
RRID:SCR_005997). Functional data will undergo motion correction, coregistration with the structural (T1w) image, segmentation/spatial normalization, and spatial smoothing (8 mm full-width at half maximum Gaussian kernel). Segmentation/spatial normalization for T1w data will use DARTEL registration to the MNI152 template, using the CAT12 toolbox (^4^
RRID:SCR_019184). During the segmentation, white matter, gray matter and cerebrospinal fluid will be isolated; WM will be masked out from the functional analyses. Normalized images will be resliced to 1.5 mm (isotropic). The resulting deformation field will be applied to the functional images.

##### FDG-PET Analysis

For FDG-PET data, an in-house whole-brain mask will be used as the explicit mask. PET images will be proportionally scaled to each image’s global values for statistical analysis. For both walk only and DT-walking conditions FDG-PET, ordinal trend/canonical variate analysis [OrT/CVA (Habeck et al., 2005)] will be applied to characterize the normal DT-walking-related brain metabolic pattern (NDWP), by comparing FDG-PET of single-walking vs. DT-walking in the healthy controls. First, the OrT transforms the preprocessed image data to increase the salience of ordinal trend effects, allowing the proceeding principal component analysis (PCA) to identify principal components with targeted expression (i.e., a consistent increase of pattern expression at the individual subject level), while also controlling for the salience of untargeted expression (Habeck et al., 2005). The principal components that result from the OrT can either be used individually, or can be linearly combined, allowing the expression of a given metabolic pattern to be quantified in each scan. Similarly, the PD-specific DT-walking-related brain metabolic pattern (PDWP) will be produced (i.e., DT-walking vs. single-walking in PD patients at pre-intervention). Additionally, we will examine if there is a different metabolic pattern, specific to the 10-week treatment-induced clinical benefits in PD by OrT/CVA (post- vs. pre-intervention during DT-walking). The topographical rating scale of the proposed FDG-PET patterns (i.e., NDWP, PDWP, and longitudinal pattern) will be computed in each FDG-PET image. Furthermore, behavioral scores (such as gait and cognitive performance) will be correlated with changes in metabolic patterns from pre- to post-intervention. The topography of the resulting spatial patterns will be compared using similarity test correcting for auto-correlation (Ko et al., 2014b).

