## Methods

### Objectives

The aim of the proposed study is twofold. Behavioral analysis of gait and cognitive function together with PET and MRI brain imaging methods will be used to evaluate the molecular basis and neural underpinnings of (1) the decline of mobility function in PD, and (2) the effects of an engaging, cognitive game-based DT-walking program on mobility functions.

The first objective is to determine if the metabolic brain activity during single and DT treadmill walking is different in PD as compared to able-bodied age-matched controls. It is hypothesized that there will be significant changes in brain metabolic activity of several cortical and subcortical regions of the PD patients relative to able-bodied controls. This will be the case for both single and DT-walking conditions.

The second objective is to conduct a multi-centered, single-blind, randomized, two-arm, and parallel group-controlled trial and examine the effects of a 10-week DT treadmill training program: on (a) gate and cognitive function tested under single and DT conditions, (b) the pattern of metabolic brain activity quantified with single and DT-walking uptake periods, and (c) structural and functional changes (at rest) occurring prior to and after DT-walking training.

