For the neuroimaging data, Aim 1 will use PET data to compare levels of metabolic activity by region between; (a) single-walk only and DT-walk trials, and (b) PD and able-bodied age-matched controls. Aim 2 will use PET and MRI (RS-fMRI, pCASL, and DTI) data to investigate neural changes (whole-brain and ROIs) between pre- and post-intervention. See Table 1 for the ROIs to be used in the PET and RS-fMRI data for Aims 1 and 2. Paired sample *t*-tests will be conducted for these different neuroimaging modalities, with age and gender included as regressors of no interest. Additional correlational analyses are planned to investigate the relationship between changes in neural activity and behavioral metrics such as cognitive task performance and gait measures.

**TABLE 1 T1:** Regions of interest for the PET and fMRI ROI analyses.

**Amygdala, L**	**Dorsolateral PFC, L**	**Inferior Temporal, R**	**Mesial Temporal, L**	**Orbital frontal, R**	**Thalamus, R**
Amygdala, R	Dorsolateral PFC, R	Insula, L	Mesial Temporal, R	Putamen, L	Uncus, L
Anterior Cingulate, L	Frontal pole, L	Insula, R	Midbrain	Putamen, R	Uncus, R
Anterior Cingulate, R	Frontal pole, R	Lateral Temporal, L	Middle Temporal, L	Substantia nigra	Ventral Striatum, L
Subgenual cingulate (BA 25)	Hippocampus, L	Lateral Temporal, R	Middle Temporal, R	Superior Temporal, L	Ventral Striatum, R
Caudate, L	Hippocampus, R	Medial PFC, L	Occipital	Superior Temporal, R	Ventrolateral PFC, L
Caudate, R	Inferior Temporal, L	Medial PFC, R	Orbital frontal, L	Thalamus, L	Ventrolateral PFC, R

*L, left; R, right; PFC, prefrontal cortex.*

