## Anticipated and Preliminary Results

The anticipated results of this study can be broken down by objective. First, in comparing if and how metabolic brain activity differs during single and DT-walking in PD patients, compared to able-bodied controls, we will likely observe increased activation of sensorimotor and cerebellar brain regions and decreased activation in the PFC of the PD patients. We hypothesize that these changes in brain activation patterns will be associated with decreased gait and cognitive performance measures and the magnitude of DT effects. Second, we hypothesize that both training programs will result in significant improvements in gate and cognitive function with medium to large effect sizes, and that the DT training program will result in significantly greater improvements in the XG compared to CG, also with medium to large effect sizes. It is hypothesized that the DT treadmill-training program will result in specific and significant changes of the DT gait-related abnormal brain metabolic pattern observed in Objective 1.

Our behavioral and PET hypotheses are supported by a recent feasibility study that we completed in which 15 PD patients (Hoehn and Yahr stages II-III) participated in a 10-week DT-treadmill gait training program using the VMT and VCG as described in the “Methods” section above (Mahana et al., 2021). Significant improvements in the majority of gait variables (average and COV of SL and SW) with medium to large effect sizes were observed following the intervention. This was the case for both walk-only and DT-walking assessments. There were also significant improvements in VMT and VCG outcome measures post-intervention with medium to large effect sizes. This was the case when tested while sitting and while treadmill walking. In addition, a qualitative analysis of the participant’s experiences revealed that the program was challenging and required a high degree of mental processing. The majority of participants reported that the games were engaging and they appreciated the variety of games used for the DT training. Also, to note 3 of the 15 participants did not like playing the games.

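### No FDG-PET pattern contrasts PD with controls, so the abnormal pattern that training is predicted to change is not among those defined and scored

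*Protocol article*

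**What the plan says.** Under Objectives, the first aim is to find out whether "metabolic brain activity during single and DT treadmill walking is different in PD as compared to able-bodied age-matched controls". The Abstract likewise makes the comparison with controls the means of finding regions that are abnormally low or high. For the trial itself, Anticipated and Preliminary Results predicts "specific and significant changes of the DT gait-related abnormal brain metabolic pattern observed in Objective 1".

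The FDG-PET Analysis section then defines three patterns:

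- The normal pattern (NDWP) is derived "by comparing FDG-PET of single-walking vs. DT-walking in the healthy controls".
- The second is defined as follows: "the PD-specific DT-walking-related brain metabolic pattern (PDWP) will be produced (i.e., DT-walking vs. single-walking in PD patients at pre-intervention".
- The longitudinal pattern is meant to be "specific to the 10-week treatment-induced clinical benefits in PD by OrT/CVA (post- vs. pre-intervention during DT-walking").

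On their use: "The topographical rating scale of the proposed FDG-PET patterns (i.e., NDWP, PDWP, and longitudinal pattern) will be computed in each FDG-PET image". On how they relate: "The topography of the resulting spatial patterns will be compared using similarity test correcting for auto-correlation".

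Separately, the imaging part of Statistical Analyses plans a regional Aim 1 comparison that includes "PD and able-bodied age-matched controls". According to the Figure 1 caption, the only PET scan after training is a DT scan.

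**The concern.** The training hypothesis needs a pattern that measures how PD differs from controls. Of the three defined, one uses controls only, one uses PD patients only before training, and one uses PD patients only before and after training. The PDWP is the nearest candidate by name, but a DT-versus-single contrast within patients captures everything the game adds to walking. That includes the response a healthy person would also show.

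The consequence is for interpretation. If the PDWP score is read as the abnormal pattern, a fall could mean that disease-related activity receded or that normal task activation was lost. A rise could mean that a deficit recovered. A flat score could hide recovery in two regions with opposite signs. The article itself expects mixed signs: higher sensorimotor and cerebellar activity and lower prefrontal (PFC) activity in PD.

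**Working it through.** The plan gives no figure to reproduce here, so the check is algebraic.

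**Set-up.** Let N be the normal DT-minus-single response across regions and D the deviation of PD patients from it.

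- The NDWP estimates N.
- The PDWP estimates N + D.
- A PD-versus-control pattern estimates D.

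A score is the projection of a scan on the pattern, scaled to unit length. Suppose training removes D completely from the DT scan. The score changes are then:

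- PDWP: −D·(N+D) / |N+D|
- NDWP: −D·N / |N|
- PD-versus-control pattern: −D·D / |D| = −|D|

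**Assumed values** (none is in the documents): 40 task-engaged regions with N = 1 in each. D equals a in 10 PFC regions, b in 10 sensorimotor regions and 0 in the other 20. Then:

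- −D·(N+D) = −10[a(1+a) + b(1+b)]
- |N+D| = √(20 + 10(1+a)² + 10(1+b)²)
- |N| = √40 = 6.32
- |D| = √(10a² + 10b²)

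| a (PFC) | b (sensorimotor) | PDWP change | NDWP change | PD-versus-control change |
|---|---|---|---|---|
| −0.6 | 0 | 2.4/5.62 = +0.43 | 6/6.32 = +0.95 | −1.90 |
| 0 | +0.6 | −9.6/7.46 = −1.29 | −6/6.32 = −0.95 | −1.90 |
| −0.6 | +0.6 | −7.2/6.87 = −1.05 | 0 | −2.68 |
| −0.6 | +0.2 | 0/6.00 = 0.00 | 4/6.32 = +0.63 | −2.00 |
| −0.2 | +0.6 | −8.0/7.21 = −1.11 | −4/6.32 = −0.63 | −2.00 |

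Every row is the same event, complete recovery. The PDWP score rises, falls or stands still. The NDWP score does not settle the matter, since it too changes sign and is zero in the third row. Only the PD-versus-control score moves the same way throughout.

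**No abnormality at all.** With D = 0 the PDWP equals N, so its cosine with the NDWP is 1.00. The analysis would still deliver a pattern labelled PD-specific. In the five rows above the cosine is 0.92 to 0.98, so under these assumptions the PDWP is mostly normal task response.

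**Noise.** A simulation with 52 patients, 15 controls and an assumed SD of 0.5 per region and scan gave PDWP changes of +0.42, −1.28, −1.04, −0.01 and −1.11. The PD-versus-control changes were −1.57, −1.56, −2.42, −1.67 and −1.68. They are smaller than the exact values because that pattern is itself estimated with error.

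**Limits.** The illustration uses simple mean contrasts, not OrT/CVA, and ignores the planned scaling to each image's global value. It shows that the sign is not fixed; it does not estimate an effect in this trial.

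**The case against.** The strongest reply is that nothing in the article equates the PDWP with the abnormal pattern. The labels normal and PD-specific may only name the group each pattern comes from. The hypothesis speaks of specific and significant changes, not of normalisation, and any change would meet that wording. Objective 1 also has its own route, the regional PD-versus-control comparison. All three patterns are scored in every scan, so PD expression of the NDWP and control expression of the PDWP will both be available. Finally, this is a condensed article.

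Much of this stands. A reader might infer that the plan declares the PDWP score its measure of normalisation, or that similarity of topography is the only link between patients and controls. The text supports neither.

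It does not close the gap:

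- If the PDWP is not the abnormal pattern, no defined pattern is, and the hypothesis has nothing to refer to.
- The regional comparison yields regions, not a pattern score. The only test named there is the paired t-test, which does not fit independent groups; that is a separate matter.
- The similarity test says how alike two patterns are but does not isolate or score the difference.
- No joint reading of the NDWP and PDWP scores is stated.
- The definition is explicit and the three patterns are enumerated, so this is not a detail left to a fuller document.

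**Conclusion.** The point holds as a mismatch between the stated hypothesis and the defined scores. The hypothesis concerns a PD-versus-control abnormality, no pattern in the FDG-PET Analysis section contrasts PD with controls, and the PDWP's change has no fixed direction under recovery. This follows from the definitions and needs no assumption beyond the PDWP containing the normal task response as well as any deviation.

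Its size cannot be stated. The documents give neither the effects nor the overlap of the two patterns, so no percentage dilution of the score can be defended, and the figures above are illustrative only. It would also go too far to conclude that the trial cannot address the hypothesis: the scans needed are already planned, and the regional comparison gives partial information. This is an inexpensive improvement to the analysis, not a flaw in the design.

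**What to change.** In the FDG-PET Analysis section:

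1. Add one abnormal pattern derived at baseline from PD versus controls. Use either the group-by-condition contrast (DT minus single-task, PD against controls) or the DT scans alone, and fix the choice in advance. The DT-only version also carries disease differences unrelated to the dual task.
2. Use a between-group pattern method. OrT/CVA as described looks for a consistent change within each person, which a comparison of different people does not offer.
3. Handle site. All 15 controls are at site 1, while 26 of the 52 patients are at site 2. Derive the pattern from site 1 patients, or state another way of separating site from disease.
4. Score the pattern in the pre- and post-intervention DT scans, state which direction counts as movement towards controls, and compare the change between XG and CG. The between-arm comparison matters because baseline scans used to derive a pattern tend to score high on it, in both arms alike.
5. Keep the PDWP as a within-PD task pattern without the PD-specific label. Test whether its baseline expression differs between PD and controls, with scores not fitted to the same scans, and read it beside the NDWP score already planned.

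The cost is revised wording and some extra analysis of scans already planned. The main drawback is precision: with 15 controls the new pattern will be estimated less well than a within-PD contrast.

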**FIGURE 1 F1:**
[figure not shown]
Experimental timeline. Assessment days (ADay) indicate order of assessments. PET scans on ADay_3_ and ADay_4_ will be counterbalanced between a single-task treadmill walking only task and a DT treadmill walking and cognitive game condition. A final DT PET scan will be acquired following intervention (ADay_7_). MRI scans will be collected pre- (ADay_2_) and post-intervention (ADay_6_). Behavioral testing (Behav; including motor measures and neuropsychological testing) will occur on three occasions: prior to intervention (ADay_1_), following intervention (ADay_5_), and again after a 6-month follow-up. Fall-history and physical activity tracking will be acquired throughout, until 12-months post-intervention. Measures of gait will be acquired throughout the program, including during behavioral assessment days, at each training session, and on PET assessment days. The experimental (XG) and control arm (CG) groups will complete the entire timeline, while healthy controls (HC) will complete up until ADay_4_.

Participants in the CG group will complete 10 weeks of a “single-task” exercise program including videogames only (i.e., for 10 min while sitting) and walking-only on the treadmill—these tasks are conducted independently, one at a time. Participants in the XG will perform various cognitive computer games during the warm up period on the compliant surface and during all treadmill walking intervals. The computer games will be played using the head mounted IB-mouse as described above. Many inexpensive and easily accessible common and modern games exist which are visually rich, fun, and engaging. They include a variety of tasks that require; (i) visual search and tracking of multiple targets, (ii) speed accuracy requirements, (iii) presence of distracters, (iv) matching tasks, and (v) working memory. Note that the games that will be used during behavioral and PET assessments and those used in the XG exercise program are different.

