#### Image Acquisition

##### PET Data

All subjects will undergo two pre-intervention [^18^F] FDG-PET scans after fasting for at least 6 h before scanning. A head CT scan will be acquired for attenuation correction purposes. Static images (10 min) will be acquired starting 40 min after injection. During the FDG uptake period, participants will perform in different sessions, on different assessment days; (a) treadmill walking only (test session 1) and (b) DT treadmill walking (test session 2; see Figure 1). The order of the walk-only and DT-walking sessions will be counterbalanced. The single and DT treadmill walking will be done for 28 min each. This will involve seven 3-min walk intervals with 1-min rest periods (standing). Walking speed and duration will be carefully controlled, and repeated for each test session (i.e., single and DT conditions, pre- and post- intervention). Seven different standardized cognitive games will be selected for the seven DT-walking intervals. These will include; (a) five 3-min VC games with different difficulty levels (i.e., increasing game speed, adding distractors, and changing path of target motions), and (b) two 3-min VMT games, one played using horizontal head rotations and one with vertical head rotations. The PD patients will repeat the DT-walking PET imaging protocol after completion of the 10-week exercise program.

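### The FDG-PET pattern labelled specific to treatment-induced benefit is derived from post- versus pre-intervention scans alone, so repeat exposure or elapsed time can produce it without any treatment benefit

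*Protocol article*

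**What the plan says.** The FDG-PET Analysis section of the protocol article derives three metabolic patterns by ordinal trend/canonical variate analysis (OrT/CVA). The third is described as "a different metabolic pattern, specific to the 10-week treatment-induced clinical benefits in PD by OrT/CVA (post- vs. pre-intervention during DT-walking"). The same section says what the method targets: "a consistent increase of pattern expression at the individual subject level". It then has the pattern score computed in every FDG-PET image, where the third pattern is simply called longitudinal, and adds that "behavioral scores (such as gait and cognitive performance) will be correlated with changes in metabolic patterns from pre- to post-intervention".

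Under PET Data, "The PD patients will repeat the DT-walking PET imaging protocol after completion of the 10-week exercise program", and "Walking speed and duration will be carefully controlled, and repeated for each test session". On session order, "The order of the walk-only and DT-walking sessions will be counterbalanced"; this concerns the two pre-intervention scans. The Figure 1 caption places the final DT scan after the intervention (ADay7) and states that "healthy controls (HC) will complete up until ADay_4".

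Under Statistical Analyses, the neuroimaging comparisons are paired t-tests "with age and gender included as regressors of no interest". Objective 2(b) is to examine, in the randomised trial, the effect of DT training on the pattern of metabolic activity.

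**The concern.** The label makes two claims: that the pattern arises from treatment, and that it tracks clinical benefit. As stated, the derivation uses only the DT-walking scans and their time order. Anything that moves the same way from pre to post in most patients meets its criterion, whether or not it has to do with treatment or benefit.

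Several such influences are plausible here: familiarity with the scan task, habituation to the PET session, and ten weeks of elapsed time. If one of them is present, the trial could report it as the neural signature of treatment benefit. Cross-validation would not expose this, because the rise would be real and reproducible but not attributable to treatment. The randomised control arm (CG) undergoes the same repeat scan and could separate shared influences from DT training, but no stated PET analysis uses it.

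**Working it through.** The plan gives no figure on this point to reproduce. The check sets the label against the derivation and the scan schedule, then shows the size of the problem under stated assumptions.

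**1. What enters the derivation.**
- Scans: DT-walking FDG-PET in PD, pre and post.
- Target: a within-patient rise between the two ordered scans.
- Arm: not named. The text says PD and does not say whether XG and CG are pooled.
- Clinical change: not named. Behavioural scores come in afterwards, as a correlation.

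**2. What differs between the pre and post scans besides treatment.**
- The post scan is always the third PET session. The pre DT scan is the first or second, by counterbalancing. Pre/post order itself cannot be counterbalanced.
- Task, speed and duration are held constant, so the post scan repeats a task already performed.
- The Intervention Protocol gives CG ten minutes of seated play with the head-mounted mouse, expressly as practice for DT assessment. Practice therefore accrues in both arms.
- Healthy controls have no post scan, so no untrained group shows the repeat-scan effect.

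**3. Whether another stated PET analysis uses arm.** The paired t-tests name only age and gender as covariates. The between-group comparison under RS-fMRI Analyses concerns graph metrics, not PET.

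**4. Illustration of size.** Assume no treatment effect and a shift of d SD of change, equal in both arms. With 52 randomised and the plan's 10% drop-out, 52 × 0.90 = 46.8, taken as 47. The pooled test is a one-sample t-test on change, two-sided at 0.05. Its noncentrality is d√N and its rejection rate is P(|T| > t(0.975, N−1)).

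| d (assumed) | N = 47: d√47 | N = 47: rate | N = 52: rate | N = 24 (about one arm): rate |
|---|---|---|---|---|
| 0 | 0 | 5% | 5% | 5% |
| 0.2 | 1.37 | 27% | 29% | 16% |
| 0.4 | 2.74 | 77% | 81% | 47% |
| 0.6 | 4.11 | 98% | 99% | 80% |
| 0.8 | 5.48 | 99.97% | 99.99% | 96% |

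A two-sample t-test of change, XG against CG, has expected difference d − d = 0, so its rate is 5% in every row. The last column shows that using one arm alone would not remove the problem.

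**5. A simulation closer to the method.** Principal components of the post-minus-pre images were combined for a consistent increase and tested by sign-flip permutation. It assumed 400 voxels, 4 components, 199 permutations and 400 runs per setting, with no arm difference and no benefit.

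| Shared shift (between-subject SD) | Pattern significant, 12 per arm | Pattern significant, 24 per arm |
|---|---|---|
| 0 | 3% | 3% |
| 0.5 | 37% | 71% |
| 1.0 | 94% | 100% |
| 1.5 | 100% | 100% |

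On the same data the XG-versus-CG test of change was significant in about 3% to 5% of runs. Correlation of pattern change with an unrelated score was significant in about 4% to 7%.

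**The case against.** **Clinical benefit does enter, one step later.** This stands in part. Every scan is scored, and behavioural scores are correlated with pattern change. In the simulation that correlation did not create a false link when benefit was independent of practice. But it comes after the pattern has been derived and labelled, it uses no arm, and it can be confounded if practice drives both the scan change and the scores.

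**An arm comparison may sit in the full plan.** Possibly: Objective 2(b) implies one, and XG-versus-CG contrasts are hypothesised for other modalities. The point does not rest on that omission. The article states the contrast and the specificity claim together, and the contrast cannot support the claim.

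**An XG-versus-CG derivation would change the question.** This stands. CG is an active programme, and the article expects both programmes to bring improvement. A pattern derived only on the arm contrast would cancel their shared benefit. The pre-post derivation should therefore be kept.

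**The post scan is not a clean second exposure.** A reader might infer from the PET schedule that patients meet the games only twice. The documents do not support that: the VMT and VCG modules are also part of behavioural testing on ADay1 and ADay5. The pre scan is not game-naive, which may reduce the familiarity effect. It does not remove the session-order or elapsed-time difference.

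**The magnitudes follow from assumed shifts.** Correct. At zero shift the pooled test is sound.

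**Conclusion.** The point holds in a limited form. The stated contrast cannot separate treatment benefit from repeat exposure or elapsed time, so specificity to treatment-induced benefit is more than it can show.

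A reader might go further and infer that the pattern will be an artefact. The documents do not support that. They give no size or direction for a repeat-scan effect, so the supported statement is that such an effect can produce the pattern. Nor do they support saying that clinical benefit is ignored, since the later correlation is planned.

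The size, 77% to more than 99% against 5%, rests on an assumed shared shift of 0.4 to 0.8 SD, on pooling of the arms at N = 47, and on a t-test standing in for OrT/CVA. With an assumed 0.2 SD the pooled rate is 27%. The 5% for the arm contrast requires the shift to be equal in both arms.

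The consequence is confined to the interpretation of one of three PET patterns. The time-by-group analysis of behavioural outcomes is unaffected.

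**What to change.** 1. Keep the post-versus-pre OrT/CVA derivation, but call its result the longitudinal (pre-to-post) pattern throughout, in line with the term the section already uses.
2. Add a comparison between XG and CG of the change in expression of that pattern.
3. Relate the change in expression to clinical change, with arm in the model.
4. Tie the wording of conclusions to these results: specificity to DT training only if the between-arm contrast supports it, and association with clinical benefit only if the arm-adjusted relation supports it. State in the article whether the arms are pooled for the derivation.

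No new scans or scores are needed; the cost is two specified analyses and a change of wording. The downsides are that the between-arm contrast is less precise (with 24 and 23 patients, its standard error is √(1/24 + 1/23) = 0.292 SD of change, against 1/√47 = 0.146 for the pooled mean change, about twice as large) and that it does not capture benefit common to both active programmes.
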